#### Referral sources

Referral sources may vary for standard and task-shifted implementation. Recruitment of clients at standard implementation sites will be done primarily from the pool of existing clients already served by those agencies, and referrals received for other services. The resettlement agencies have a range of existing programs and services they offer to families, and families with children in the target age range already being served will be offered SafeCare services. Additional referrals may come from governmental organizations, social service organizations, healthcare providers, and ethnic group organizations.

Recruitment and referrals for services to be delivered by CHWs will be facilitated by the administrative structure of the project. That is, project staff will make connections with community-based referral agencies, advertise the study and services with the help of project stakeholders and community leaders, and direct interested participants to the CHW’s for the service. CHWs are expected to have strong connections to community organizations, social service and health agencies, childcare providers, and ethnic organizations, and those connections should facilitate service referrals. All recruitment efforts will describe the intervention service as a program designed “to build a positive relationship with your child and promote healthy development to be ready for school.”

#### Participant enrollment process

Clients who express an interest in the project will first be referred to the study coordinator for enrollment. Because of language barriers, interested participants will be instructed to call a number, leave their name and contact information, and a member of the research team who speaks the native language will return their call. A research team member will contact the interested participant and describe the full study participation, confirm eligibility and, if eligible, consent the participant and conduct the first assessment. Eligibility criteria include being over 18, being a primary caregiver of a child ages birth through five, and identifying and speaking the language of one of the targeted ethnic/national groups.

#### Assessment of implementation outcomes

We conceptualize this study as primarily an implementation study but are collecting both implementation data and family outcome data because of the unique population involved. Several metrics related to implementation will be collected: service delivery*,* provider fidelity, client skill uptake, client engagement/completion, client satisfaction/relevance, and adaptations.
*Service delivery*. Service delivery will be measured as a simple count of the number of clients served. This metric is an important indicator of the success of the implementation. The target goal for each of standard implementation and task-shifted implementation is 120 clients over 3 years of implementation (240 total clients served). Success or failure at serving clients may suggest the implementation method is viable or not.*Provider fidelity.* Fidelity will be monitored on an ongoing basis, and we expect to collect fidelity metrics monthly for the life of the study (3 years).*Client skill uptake.* As a part of SafeCare-PCI, providers observe parents interacting with children in play and routine daily activities and rate their use of the desired skills on a 3-point scale (no use, some use, proficient use).*Client engagement/completion.* Client engagement and completion will be a count of the number of sessions completed and whether each family completed the program (all 6 sessions). Note that clients will receive a $25 incentive for completing all six sessions of the intervention.*Client satisfaction.* Satisfaction will be measured via a 10-item survey given to parents at the end of the program, and a short questionnaire assessing cultural relevance of the program. Finally, brief qualitative interviews will be conducted with a subset of families (20 per year, total *n* = 60) regarding the program to determine program satisfaction, helpfulness, and effectiveness.*Adaptations.* We will document planned and ad-hoc adaptations to both the curriculum and to the implementation process for each of the standard implementation and the task shifted implementation as implementation rolls out. Adaptations will be tracked by ethnic group and will be coded and classified conceptually for reporting purposes.

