#### Assessment of family outcomes

Data will be collected from clients at three assessment points: baseline (prior to any intervention), post-SafeCare (around 6–8 weeks after baseline), and six-months after baseline. Assessments will be interviews conducted by research team members who speak the native language of the participants. Participants will receive a $25 incentive for completing each assessment. Measures to be collecting during the assessment are as follows:
Demographics – standard demographics including current work and living situation, and an assessment of migration path.*Positive Parenting Behaviors* will be assessed using the Parenting Young Children Survey, [59] a 21-item scale assessing three dimensions of parenting behaviors: limit setting, proactive positive parenting, and supporting positive behavior.*Parent-child Relationship and Child Behavioral Health* will be assessed using the attachment subscale of the Devereaux Early Child Assessment [52].*Child health status* will be assessed with the 14-item Functional Status II scale [77].*Parenting Stress* will be assessed via the Parenting Stress Index– short form [3], a 36-item scale designed to measure stressors in parenthood including parental distress, dysfunctional interactions, and stressors related to having a difficult child.*Parent trauma and trauma symptoms* will be assessed with the Harvard Trauma Questionnaire [64] a 17-item scale used to assess both experiences of trauma and trauma symptoms that has been extensively validated in refugee and international populations.*Parent mental health* will be assessed with the Hopkins Symptom Checklist [37], a 25-item scale assessing depression, anxiety, and somatic symptoms.*Social support* will be assessed with 10 items from the Protective Factors Survey [30] which includes concrete and emotional support subscales.*Family Resources* – the 40-item Family Resources Scale – Revised [91] assesses the adequacy of family needs in four domains: basic needs, money, time for self, time for family.*Post-migratory problems –* The Post Migration Living Difficulties Scale (PMLD [84];) is a scale on which respondents rate 24 stressors on the extent to which the issue has caused them problems.*Parent health status and quality of life* will be assessed with the World Health Organization, Quality of Life Scale [95] a 26-items scale assessing physical and mental health, and overall quality of life.

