##### Implementation metrics

For the implementation metrics, some data exist at the provider level (families served, fidelity), while others exist at the family level (completion of the program, skill acquisition, satisfaction, perceived cultural relevance). Provider level implementation metrics, including fidelity and adaptations, will be analyzed descriptively because of too few observations for statistical analyses. We will examine mean fidelity and patterns of fidelity over time as adaptations are made. For adaptations, we will describe qualitatively the nature of the adaptations and classify those adaptations conceptually. We will also track adaptations made by SI vs. TS providers by ethnic group. For implementation metrics that exist at the family level (program completion, program satisfaction), we will have either one measurement point (completion of SafeCare, consumer satisfaction, cultural relevance) or two (skill acquisition). For metrics with one measurement time point, analyses of differences between implementation groups will be a simple t-test for continuous variables (satisfaction, cultural relevance) or chi-square analyses for categorical variables (completion). If covariates are needed in the models because of baseline differences, a regression framework will be adopted using linear regression for continuous outcomes and logistic regression for dichotomous outcomes. For skill acquisition, which has two measurement time points, a regression framework will be adopted in which the Time 2 skills are regressed onto Time 1 skills, implementation group, and any relevant covariates.

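### Satisfaction and, on a natural reading, cultural relevance are collected once at program end, so the comparison of implementation groups rests mainly on families who stay and may be biased if completion differs

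*Protocol article*

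**What the plan says.** Under Assessment of implementation outcomes, the protocol article fixes the occasion: "Satisfaction will be measured via a 10-item survey given to parents at the end of the program". The same sentence adds "a short questionnaire assessing cultural relevance of the program" and gives it no other occasion. Completion is defined there as attending all six sessions and is itself an implementation outcome.

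Under Implementation metrics, family-level measures are said to have "either one measurement point (completion of SafeCare, consumer satisfaction, cultural relevance) or two (skill acquisition". The groups are compared by "a simple t-test for continuous variables (satisfaction, cultural relevance", with linear regression if baseline differences call for covariates. Completion is compared by chi-square.

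Under Assessment of family outcomes, the research team interviews clients at baseline, "post-SafeCare (around 6–8 weeks after baseline", and six months after baseline. The interviews are in the client's language, with a $25 incentive for each. Neither satisfaction nor cultural relevance is among the measures listed.

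**The concern.** A family that leaves after, say, session 2 does not reach the end of the program, and the article names no other occasion on which its opinion is sought. The t-test then compares the groups among families selected by something that happens after enrolment. Whether a family stays may depend on the implementation method and on how the family feels about the program. When it depends on both, the families remaining in the two groups are no longer comparable in satisfaction, even if satisfaction among all starters was the same.

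The remedies in the article do not reach this. Covariate adjustment is planned for baseline differences, and it removes the bias only if the baseline covariates explain the dropout. The chi-square on completion would show a gap in retention but would not correct the satisfaction comparison.

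The study describes itself as primarily an implementation study, and satisfaction and relevance are two of the few implementation measures it tests formally between groups. A method that keeps doubtful families to the end could score lower on satisfaction because it kept them.

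**Working it through.** **The plan's own figure.** None is given for satisfaction or cultural relevance. The stated detectable difference (d = .35–.45 with 240 families and attrition up to 20%) is for family outcomes. Alpha and power are not stated. At an assumed two-sided 5% and 80% power, (1.960 + 0.842) × √(2/n) gives 0.362 for n = 120 per group and 0.404 for n = 96. Both lie inside the stated range, and nothing below depends on it.

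**Inputs.** From the article: 120 families per group, one measurement at program end, and a two-group t-test. Assumed, because the article gives no values: the completion rate c in each group, and the correlation ρ between satisfaction and the propensity to complete (bivariate normal). True satisfaction is set equal in the two groups, and only completers are assumed to give scores.

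**Formulas.** With z(c) the standard normal quantile of c:

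- Selection factor: λ(c) = φ(z(c))/c. The mean satisfaction of completers is shifted by ρλ(c).
- Bias between groups: ρ × [λ(lower c) − λ(higher c)].
- Variance among completers: 1 − ρ²λ(λ + z(c)).
- Standard error: square root of the sum over groups of variance/(120c).
- False-positive rate: Φ(−1.96 − bias/SE) + Φ(−1.96 + bias/SE).

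**One case in full: 80% against 60%, ρ = 0.5.**

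- λ(0.8) = 0.280/0.8 = 0.350, and λ(0.6) = 0.386/0.6 = 0.644.
- Bias = 0.5 × (0.644 − 0.350) = 0.147 SD.
- Variances: 1 − 0.25 × 0.350 × (0.350 + 0.842) = 0.896, and 1 − 0.25 × 0.644 × (0.644 + 0.253) = 0.856.
- SE = √(0.896/96 + 0.856/72) = 0.146, so bias/SE = 1.01.
- False-positive rate = Φ(−2.97) + Φ(−0.95) = 0.17.

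**Range.** A positive bias favours the group with lower completion.

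| Completion | ρ | Bias (SD) | False-positive rate |
|---|---|---|---|
| 80% vs 60% | 0.3 | 0.09 | 9% |
| 80% vs 60% | 0.5 | 0.15 | 17% |
| 80% vs 60% | 0.7 | 0.21 | 33% |
| 80% vs 50% | 0.3 | 0.13 | 13% |
| 80% vs 50% | 0.5 | 0.22 | 31% |
| 80% vs 50% | 0.7 | 0.31 | 61% |
| 90% vs 80% | 0.5 | 0.08 | 9% |
| Equal completion | any | 0 | 5% |
| Any gap | 0 | 0 | 5% |
| 80% vs 60% | −0.3 | −0.09 | 9% |

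**The case against.** The strongest reply is that the article never restricts the survey to families with all six sessions. It does not say who administers it or what happens with early leavers, and a condensed article may leave that to the full protocol. That is fair as to the word completers, which is an inference. The occasion of measurement, however, is fixed in the text at program end, and no other route is given.

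Second, the size rests on assumptions. The only loss figure in the article is client attrition of up to 20%, under Family outcomes. Completion of 60% or 50% appears nowhere, and the $25 incentive for finishing all six sessions may hold completion up. A smaller gap gives a smaller bias, as the 90% against 80% row shows. This stands, and it is why a range is given.

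Third, session counts and completion are reported by group, so a retention gap would be visible, and the 60 qualitative interviews are not limited to completers. Both help interpretation, but neither corrects the t-test.

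A reader might infer more than the text supports:

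- **That second skill ratings are also taken only at program end.** The article says that "providers observe parents interacting with children in play and routine daily activities and rate their use of the desired skills" and that "Time 2 skills are regressed onto Time 1 skills, implementation group, and any relevant covariates". It does not date Time 2, which could be the last session attended. Early leavers may lack a second rating, but the text does not settle this.
- **That completion is expected to differ between groups.** It is to be tested, and no difference or direction is predicted.
- **That the group losing more families must look better.** Leaving for unrelated reasons, such as work or relocation, gives no bias, and a negative correlation changes the sign.
- **That the bias would reverse the conclusion.** The calculation assumes no true difference, so it shows no reversal. The Innovation section, moreover, asks whether high satisfaction can be attained, which is not in itself a contrast between groups.

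**Conclusion.** The point holds for satisfaction and, on a natural reading, for cultural relevance. As scheduled, both are observed mainly in families who stay, while staying is itself an outcome compared between the groups. The resulting bias is conditional: it needs unequal completion together with dropout linked to satisfaction. If less satisfied families leave more often, which is the likelier direction, the bias favours the group with the greater loss. Under the assumed gaps of 20 to 30 percentage points and correlations of 0.3 to 0.7, it is about 0.09 to 0.31 SD, and a nominal 5% test rejects about 9% to 61% of the time when there is no true difference. The article supplies neither the completion rates nor the correlation, so these figures show what could happen and are not a forecast. The change should still be made, because opinions not collected from early leavers cannot be recovered at the analysis stage.

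**What to change.** Give the 10-item satisfaction survey and the cultural-relevance questionnaire in the research-team post assessment, around 6–8 weeks after baseline, to every family that started SafeCare. State that the interview takes place on that schedule whether or not the family finished the six sessions. Make the SI against TS comparison among all starters the main analysis, and report completers only as secondary. Give the number of scores obtained by group and completion status, so that remaining losses can be seen.

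The cost is a somewhat longer interview that is already scheduled and paid for. The length of the relevance questionnaire is not stated, so the added time cannot be given exactly. Some early leavers may miss this interview too, so the change reduces the selection without guaranteeing its removal. It does not address skill ratings, which providers make during sessions.

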#### Assessment of family outcomes

Data will be collected from clients at three assessment points: baseline (prior to any intervention), post-SafeCare (around 6–8 weeks after baseline), and six-months after baseline. Assessments will be interviews conducted by research team members who speak the native language of the participants. Participants will receive a $25 incentive for completing each assessment. Measures to be collecting during the assessment are as follows:
Demographics – standard demographics including current work and living situation, and an assessment of migration path.*Positive Parenting Behaviors* will be assessed using the Parenting Young Children Survey, [59] a 21-item scale assessing three dimensions of parenting behaviors: limit setting, proactive positive parenting, and supporting positive behavior.*Parent-child Relationship and Child Behavioral Health* will be assessed using the attachment subscale of the Devereaux Early Child Assessment [52].*Child health status* will be assessed with the 14-item Functional Status II scale [77].*Parenting Stress* will be assessed via the Parenting Stress Index– short form [3], a 36-item scale designed to measure stressors in parenthood including parental distress, dysfunctional interactions, and stressors related to having a difficult child.*Parent trauma and trauma symptoms* will be assessed with the Harvard Trauma Questionnaire [64] a 17-item scale used to assess both experiences of trauma and trauma symptoms that has been extensively validated in refugee and international populations.*Parent mental health* will be assessed with the Hopkins Symptom Checklist [37], a 25-item scale assessing depression, anxiety, and somatic symptoms.*Social support* will be assessed with 10 items from the Protective Factors Survey [30] which includes concrete and emotional support subscales.*Family Resources* – the 40-item Family Resources Scale – Revised [91] assesses the adequacy of family needs in four domains: basic needs, money, time for self, time for family.*Post-migratory problems –* The Post Migration Living Difficulties Scale (PMLD [84];) is a scale on which respondents rate 24 stressors on the extent to which the issue has caused them problems.*Parent health status and quality of life* will be assessed with the World Health Organization, Quality of Life Scale [95] a 26-items scale assessing physical and mental health, and overall quality of life.

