Our study will focus on the *parent-child interaction module* (PCI) of SafeCare because it most directly addresses the type of positive, nurturing behaviors that have been demonstrated to promote positive parenting and improved children’s development outcomes and is largely a preventive intervention. The PCI module includes two separate protocols, one for parents of infants 0–12 months, and one for parents of children 1 to 5 years old. Both protocols promote positive parent-child relationships by teaching parents to attend to their children and interact with them through language, stimulating play activities, and positive verbalizations and touch. Parents of toddlers and older children are also taught to structure activities using planned activities training [78] in which parents are taught to talk with their child about activities, engage them in making choices, explain rules, provide positive reinforcers while ignoring minor misbehaviors, and give positive consequences for the child’s success [55]. Data from studies focusing only on the PCI module of SafeCare, including a randomized trial, indicates that it is effective at changing parent behavior [29, 32, 56], and child outcomes [19, 53].

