##### Family outcomes

For family outcomes, we will collect data from 240 families (120 SI and 120 TS) at three time points: baseline, post-intervention and four-month follow up (6 months after baseline). With three data points over time, family outcomes will be analyzed in a multilevel context via a GLMM framework with Time nested within Family. The goal is to examine differences in family outcomes between families served by standard and task-shifted implementation, and thus the primary independent variable will be implementation group. The primary outcomes are parent-skills, the parent-child relationship, and parenting-stress. The sample size of 240 was determined via a power analysis and plans to examine differences by implementation type. The sample size provides sufficient power to detect small-to-medium sized differences (*d* = .35–.45) between groups depending on the client attrition (up to 20%) and number of time points.

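### Infant families are taught a narrower programme than families of 1-5-year-olds, yet all are scored on one positive-parenting scale that includes limit setting, and the stated model has no child-age or protocol term

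*Protocol article*

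**What the plan says.** **Programme content.** In the section on the SafeCare model: "The PCI module includes two separate protocols, one for parents of infants 0–12 months, and one for parents of children 1 to 5 years old". The shared content is stated first: "Both protocols promote positive parent-child relationships by teaching parents to attend to their children". One group then receives more: "Parents of toddlers and older children are also taught to structure activities using planned activities training". That addition includes teaching parents to "explain rules, provide positive reinforcers while ignoring minor misbehaviors".

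**Eligibility.** Under Participant enrollment process, a participant qualifies by "being a primary caregiver of a child ages birth through five", so infant families will be enrolled. No target share by child age is given.

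**Measure.** Under Assessment of family outcomes, positive parenting is measured by "a 21-item scale assessing three dimensions of parenting behaviors: limit setting, proactive positive parenting, and supporting positive behavior". No age restriction or infant version is mentioned. The article does not say whether a total or the separate dimensions will be analysed.

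**Analysis.** Under Family outcomes: "The primary outcomes are parent-skills, the parent-child relationship, and parenting-stress", and "family outcomes will be analyzed in a multilevel context via a GLMM framework with Time nested within Family". Implementation group is the main independent variable. No child-age or protocol term appears. Under Implementation metrics, by contrast, the article does provide for covariates, including where the groups differ at baseline.

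**Design.** Aim 2 is quasi-experimental, and the section on referral sources allows these to vary between the two arms.

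**The concern.** The measure and the programme do not line up for the youngest children. The older-child content nearest to limit setting (rules and the handling of minor misbehaviour) is not described as part of the infant protocol. Infant families therefore have less programme-driven reason to change on that dimension, whoever delivers the service. Including them without distinction weakens any true SI-TS difference there.

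The second route is confounding. Allocation is not random. SI recruits mainly from existing agency clients, while TS recruits through project outreach and the community health workers' own connections. Infant share could therefore differ between arms. If parents' scores also change as children grow, part of an age effect would appear as a difference between delivery methods. Infants aged 6 months or more at baseline pass their first birthday by the six-month assessment, so such change could fall within follow-up. Adjusting for the baseline score would not remove a difference in rates of change.

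**Working it through.** **1. The plan's own figure.** The article states detectable differences of d = 0.35-0.45 with 120 families per arm and attrition up to 20%. Alpha, power and within-family correlation are not given, so the range cannot be strictly reproduced. With a two-sided 5% test at one time point, detectable d = (z for alpha + z for power) × √(2/n):

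| n per arm | 80% power | 90% power |
|---|---|---|
| 120 | 0.362 | 0.418 |
| 96 (20% attrition) | 0.404 | 0.468 |

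Averaging two post-baseline measures with correlation 0.5 (assumed) gives 0.313 (n = 120) to 0.350 (n = 96) at 80% power. The stated range is plausible, and nothing below depends on reproducing it.

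**2. Infant share q (assumed).** The documents give no age distribution. If ages were spread evenly, q = 12/72 = 16.7% (birth to the sixth birthday) or 12/60 = 20% (birth to the fifth). That is 240 × 0.167 = 40 to 240 × 0.20 = 48 families.

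**3. Dilution.** Assume that infant families show no SI-TS difference on limit setting, that the standard deviation is the same in both age groups, and that q is the same in both arms. With f the share of the analysed score that is limit setting, observed d = true d × (1 − q × f). Power is for 120 per arm, two-sided 5%, one time point, normal approximation.

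| Score | True d | Observed d (q = 16.7% to 20%) | Power, undiluted → diluted |
|---|---|---|---|
| Limit setting alone (f = 1) | 0.35 | 0.292 to 0.280 | 77% → 62% to 58% |
| Limit setting alone (f = 1) | 0.45 | 0.375 to 0.360 | 94% → 83% to 80% |
| Total score (f = 1/3, assumed) | 0.35 | 0.331 to 0.327 | 77% → 73% to 72% |
| Total score (f = 1/3, assumed) | 0.45 | 0.425 to 0.420 | 94% → 91% to 90% |

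Over a wider range of q, 10% to 40%, a total score with f = 1/3 takes d = 0.35 to 0.338-0.303.

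**4. Families on the 1-5-year protocol only.** These would number 120 × 0.80 = 96 to 120 × 0.833 = 100 per arm. At the undiluted d = 0.35, power is 68% to 70%, against 58% to 62% for all families on limit setting. Under these assumptions the smaller, better-matched set is the more sensitive one for this dimension.

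**5. Possible bias.** Spurious SI-TS difference = (difference in infant share between arms) × (age-related difference in score or change, in SD). Every input is assumed.

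- In change: a 15-point imbalance with 0.3-0.6 SD more change in infant families gives 0.15 × 0.3 = 0.045 to 0.15 × 0.6 = 0.09 SD.
- In level: a 10-20-point imbalance with a 0.3-0.8 SD gap gives 0.10 × 0.3 = 0.03 to 0.20 × 0.8 = 0.16 SD. Comparing change within families would absorb part of a stable gap of this kind.

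If infant share is equal in the two arms, or scores do not depend on child age, the bias is zero.

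**The case against.** The strongest reply is that this is a condensed article. Covariates, scoring and analysis subsets commonly sit in a full protocol or analysis plan that is not shown. Calling implementation group the primary independent variable does not exclude others. That stands as a caution: an unseen plan may already contain the term. However, the instrument, the age range and the two protocols are all fixed in this document, and it mentions covariates for the implementation metrics while naming none for family outcomes.

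Several stronger readings are tempting and should not be drawn:

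- **That infant families cannot respond on limit setting.** The SafeCare section never uses that term. The link to rules and misbehaviour is a fair inference, and the consequences it mentions are positive ones for the child's success, not discipline.
- **That a single total score will be analysed.** Scoring is left open, and the article does not expressly equate the primary parent-skills outcome with this scale.
- **That the score moves with child age.** This is plausible but undocumented.
- **That the SI-TS comparison is biased.** Providers are trained together and nothing suggests that the protocols differ by arm. A mismatch common to both arms costs sensitivity; bias needs unequal age mix as well as an age effect.

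It is also fair to say that the older-child content (planning activities, choices, positive reinforcers) overlaps the scale's other two dimensions. Dropping infant families from limit setting alone would not remove all the untaught content. For that reason the restriction belongs in a supporting analysis.

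**Conclusion.** The point holds in a limited form. One scale with a limit-setting dimension is applied to families taught two different protocols, and the stated family-outcome model does not distinguish them. The likely consequence is lost sensitivity: d = 0.35 becomes about 0.28-0.29 on limit setting, or about 0.33 on a total score with limit setting as one third. These figures rest on an assumed infant share of 17-20% and on no SI-TS difference on limit setting in infant families. Bias is a conditional risk that the non-random design permits; at the assumed inputs it is 0.03-0.16 SD, below the stated detectable range of 0.35-0.45. The point does not invalidate the comparison, but it justifies a small and specific improvement to the model.

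**What to change.** 1. Define one index child per family at enrolment, and record which protocol (infant or 1-5 years) is delivered.
2. In the family-outcome GLMM, include protocol stratum, or baseline child age, and its interaction with time. This guards against unequal age mix between the arms. It does not by itself undo the dilution.
3. Report the limit-setting dimension in families on the 1-5-year protocol as a supporting analysis, and keep all families in the main analysis. This addresses the dilution.
4. State whether the scale is analysed as a total or by dimension, and whether it is the measure behind the primary parent-skills outcome.

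If an existing analysis plan already does this, one sentence saying so is enough.

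**Cost.** Wording, one recorded field and two model terms. Child age should already be available from the eligibility check. The supporting analysis would use about 20% fewer families (assumed), roughly 192-200 of 240 before attrition.
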